### Definitions

#### Comparator Group (Standard of Care)

Currently, APRI and FIB-4 scores are not routinely reported anywhere in Australia. Prior to the intervention, blood tests will be reported per standard of care. APRI and FIB-4 scores will be calculated automatically by the pathology service from the start of the study but will not be reported to ordering clinicians until the intervention period. FibroScans are requested through a paper-based referral form by general practitioners or specialists, which is then faxed to the hospital for triage and booking.

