#### Intervention (In Addition to Standard of Care)

St Vincent’s Pathology automatically calculates and reports APRI and FIB-4 scores if platelet count, alanine transferase (ALT) level, and AST level are requested together in a single blood test by primary care physicians. This is provided free of charge. The result will be reported to the requesting primary care physician (both in paper format and online), along with a brief interpretation of the APRI and FIB-4 results, their relevance to liver cirrhosis screening, and a web link for further web-based information. No additional testing or appointments are scheduled as part of this study in addition to the standard of care.

Two separate pathways will be used by St Vincent’s Pathology to notify clinicians of our new APRI and FIB-4 reporting format approximately 1 month prior to the commencement of the intervention period. (1) The St Vincent’s Pathology standard liver function test result report will include a comment stating that APRI and FIB-4 scores will be reported as of the date of project commencement. (2) There will be a new banner included on the St Vincent’s Pathology website notifying clinicians of the availability of automatic reporting of APRI and FIB-4 scores on blood test events and the date that this reporting will commence. This will have a web link to further information on the APRI and FIB-4 score, as well as information about chronic liver disease.

The additional information on the website includes (1) how APRI and FIB-4 are calculated and how it is used, (2) how to interpret the APRI and FIB-4 result, (3) what further tests would be recommended if someone has an abnormal APRI result, (4) further general information about chronic liver disease and liver cirrhosis, and (5) a link to a web-based referral form for the St Vincent’s Hospital FibroScan service to book a confirmatory FibroScan to determine whether the patient has liver cirrhosis.

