#### Intervention Period

From February 1, 2024, to July 31, 2024, St Vincent’s Pathology will commence inclusion of automatic calculation of APRI and FIB-4 score reporting on all pathology blood testing events where an AST, ALT, and platelet count are ordered. St Vincent’s Pathology will provide for these testing events: (1) the APRI result, (2) the FIB-4 result, (3) an explanation of what APRI and FIB-4 measure and what cutoffs are used to define cirrhosis, and (4) recommendations for further investigation of elevated APRI or FIB-4 with transient elastography (FibroScan) and performance of a liver disease screen if underlying liver disease is not known. In addition, a web link to the St Vincent’s Pathology website for liver disease and cirrhosis information page will be included on all blood test reports where APRI and FIB-4 are calculated, with a provided URL link to a unique St Vincent’s Hospital FibroScan referral form. This link will be distinct from the standard fax-based St Vincent’s FibroScan referral form to allow measurement of referrals specifically generated in response to St Vincent’s Pathology APRI or FIB-4 score calculations during the study period.

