### Statistical Analysis Plan

#### Outcome Measures

Data will be analyzed per test event and per individual tested.

Primary outcomes of this study include the number of APRI and FIB-4 scores calculated on blood test events conducted during the study period, overall and per month; the number (proportion) of APRI scores that are greater than 1.0 and FIB-4 scores that are greater than 2.67; number of FibroScan referrals overall and per month, operationalized as number of completed FibroScan referrals generated online using the recommended St Vincent’s Pathology FibroScan referral link on the request slip, or St Vincent’s Pathology APRI or FIB-4 calculation web page referral form link; number of individuals with an APRI greater than 1.0 or FIB-4 score greater than 2.67 who undergo a FibroScan test at St Vincent’s Hospital Melbourne overall and per month; proportion of individuals with an APRI greater than 1.0 or FIB-4 score greater than 2.67 who undergo a FibroScan test at St Vincent’s Hospital Melbourne; the number of individuals per month who undergo FibroScan at St Vincent’s Hospital Melbourne who have cirrhosis diagnosed (liver stiffness measurement >12.5kPa); the number (proportion) of individuals with an APRI greater than 1.0 or FIB-4 score greater than 2.67 who have cirrhosis confirmed by FibroScan; the number (proportion) of individuals with etiology-specific cirrhosis range FibroScan results that are referred to the specialist liver clinic; and the number (proportion) of individuals with etiology-specific cirrhosis range FibroScan results that attend to the specialist liver clinic appointment.

The secondary outcomes of this study include the number (proportion) of individuals, stratified by age category, sex, and postcode who have elevated APRI greater than 1.0 and FIB-4 score greater than 2.67, attend the FibroScan clinic for further testing, have etiology-specific cirrhosis range FibroScan scores (kPa), and attend a liver specialist clinic appointment.

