### Analysis Methods

The number of APRI and FIB-4 scores generated and the proportion of APRI and FIB-4 scores in the cirrhosis range will be described overall and rates per month will be calculated.

The number (proportion) of individuals with an elevated APRI or FIB-4 who are referred for a FibroScan will be described overall and per month; and the number of FibroScan referrals after the intervention will be compared with the number of FibroScan referrals prior to the intervention by logistic regression modeling (time series analysis with the timepoint of interruption defined as February 1, 2024, when the reported APRI score intervention was introduced).

Similarly, the number (proportion) of individuals with an elevated APRI or FIB-4 who are referred for a FibroScan and who attend their FibroScan appointment, overall and per month, will be described and compared with the number (proportion) of FibroScan appointments attended prior to intervention using linear regression modeling, as well as the number (proportion) of individuals with FibroScan results in cirrhosis range that are referred and attend specialist liver clinic appointments.

The number and proportion of individuals with an elevated APRI or FIB-4 who had cirrhosis confirmed by FibroScan will be described, and sensitivity, specificity, and positive and negative predictive values of APRI for cirrhosis determined by confusion matrix. The area under the receiver operating characteristic curve of APRI and FIB-4 for cirrhosis diagnosis will also be calculated by receiver operating characteristic analysis.

The bivariate distribution of sociodemographic (sex, age category, and urban or regional place of residence [defined by postcode using SEIS data]) and clinical variables (liver disease indication) within the proportion of people with elevated APRI and FIB-4 score, who attend FibroScan testing, have elevated FibroScan results, and attend the liver specialist clinic will be determined and compared with their counterparts using chi-square test for categorical data, 2-tailed Student *t* test for parametric continuous data, and Wilcoxon rank-sum test for nonparametric continuous data as appropriate.

A 2-tailed *P* value of .05 will be used as the significance threshold for all analyses. All analyses will be performed using STATA (version 17; Stata Corporation).

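### Sensitivity, specificity and AUROC of the fibrosis scores will be biased, because an elevated score itself prompts the FibroScan that establishes cirrhosis

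*Protocol article*

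**What the plan says.** All references are to the protocol article.

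- **Accuracy measures.** Analysis Methods commits to "sensitivity, specificity, and positive and negative predictive values of APRI for cirrhosis determined by confusion matrix" and adds: "The area under the receiver operating characteristic curve of APRI and FIB-4 for cirrhosis diagnosis will also be calculated". The confusion matrix is for APRI only; FIB-4 enters through the AUROC.
- **Reference standard.** Outcome Measures defines cirrhosis by FibroScan, with liver stiffness above 12.5 kPa. No other source of cirrhosis status is described.
- **Who is scanned in the intervention period.** According to Intervention Period, the report carries "recommendations for further investigation of elevated APRI or FIB-4 with transient elastography (FibroScan").
- **Scans arranged by the study.** None: "No additional testing or appointments are scheduled as part of this study in addition to the standard of care" (Intervention section).
- **Who is scanned under usual care.** "FibroScans are requested through a paper-based referral form by general practitioners or specialists" (Comparator Group). The scores are calculated but not shown to clinicians in the preintervention period.
- **Caveats.** Analysis Methods gives no restriction, correction or caveat for partial verification, and Strengths and Limitations does not mention it.

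**The concern.** A confusion matrix needs both the score and the disease status of each person. Status exists only for those scanned, so the table can hold only scanned people. In the intervention period the index test helps decide who they are, since elevated scorers are steered to FibroScan and low scorers are not. This is partial verification that depends on the index test. It over-represents score-positives in the table, which raises apparent sensitivity and lowers apparent specificity.

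Sensitivity is the figure that bears on missed cirrhosis. The article's background presents these scores as tests that exclude cirrhosis in people with chronic liver disease. A near-perfect sensitivity from this table could be read as support for that use in the screened population, when cirrhosis below the cutoff has mostly not been looked for.

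**Working it through.** **Inputs from the article (Results, Table 1).** 37,872 individuals, of whom 446 had APRI above 1 and 816 had FIB-4 above 2.67. These reproduce: 446/37,872 = 1.18% (stated 1.2%) and 816/37,872 = 2.15% (stated 2.2%). APRI-negatives number 37,872 − 446 = 37,426, or 98.8%.

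**Assumed inputs (not in the article).** PPV 25%; cirrhosis in 0.25% of APRI-negatives; 30% of APRI-positives and 0.5% of APRI-negatives scanned.

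**Step 1: whole cohort.**

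| | Cirrhosis | No cirrhosis | Total |
|---|---|---|---|
| APRI > 1 | 446 × 0.25 = 111.5 | 334.5 | 446 |
| APRI ≤ 1 | 37,426 × 0.0025 = 93.6 | 37,332.4 | 37,426 |

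Sensitivity = 111.5/(111.5 + 93.6) = 54.4%. Specificity = 37,332.4/(37,332.4 + 334.5) = 99.1%.

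**Step 2: scanned people only** (first row × 0.30, second row × 0.005).

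| | Cirrhosis | No cirrhosis |
|---|---|---|
| APRI > 1 | 33.45 | 100.35 |
| APRI ≤ 1 | 0.47 | 186.66 |

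Apparent sensitivity = 33.45/(33.45 + 0.47) = 98.6%. Apparent specificity = 186.66/(186.66 + 100.35) = 65.0%. PPV stays at 33.45/133.8 = 25% and NPV at 186.66/187.13 = 99.75%, because each row is scaled by a single factor.

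**Step 3: Begg-Greenes correction.** Apply the scanned-row cirrhosis proportions (0.25 and 0.0025) to the known row totals. Sensitivity = (0.25 × 446)/(0.25 × 446 + 0.0025 × 37,426) = 54.4%, and specificity returns to 99.1%.

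**Step 4: range.** With PPV of 20 to 30%, cirrhosis in 0.1 to 1% of APRI-negatives and 0.5% of negatives scanned, whole-cohort sensitivity is 19 to 78% and specificity about 99%. In the scanned:

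| Positives scanned | Apparent sensitivity | Apparent specificity |
|---|---|---|
| 10% | 83 to 99% | 84 to 86% |
| 30% | 94 to 99.5% | 63 to 67% |
| 50% | 96 to 99.7% | 51 to 55% |

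With equal uptake in both rows (2% was tried) there is no bias.

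**Step 5: AUROC.** In a simulation with normally distributed scores, 1.8 SD separation and 0.5% prevalence (all assumed), the full-cohort AUROC is 0.90. In the scanned it is about 0.92, 0.86 and 0.83 at 10%, 30% and 50% uptake in positives, with 0.5% of negatives scanned. It can move either way.

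**Step 6: selection on clinical suspicion.** Keep Step 2, but let APRI-negatives with cirrhosis be scanned at 5% or 10% instead of 0.5%. NPV falls from 99.75% to 97.6% or 95.2%. Apparent sensitivity becomes 87.7% or 78.1%, still well above 54.4%.

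**The case against.** Several points on the other side stand and limit the finding.

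- **Predictive values.** A reader might infer that all four confusion-matrix figures are spoiled by score-driven referral. They are not: if the score alone decides who is scanned, PPV and NPV are unbiased (Step 2). They are distorted only to the extent that clinicians choose people on suspicion of disease, which usual referral allows (Step 6 shows this for NPV).
- **Composition of the table.** A reader might take the matrix to include only people with an elevated APRI or FIB-4, which would leave specificity and NPV without a screening meaning. In the Analysis Methods sentence that restriction attaches to the count of confirmed cases; the accuracy clause does not carry it.
- **Low scorers.** It would be too strong to say that none are scanned. Usual referral continues, and the web link appears on every report with calculated scores. What is absent is a low-score sample scanned by design.
- **Plausible inputs.** False positives cannot exceed 446, so at low prevalence APRI specificity is at least about 1 − 446/37,872 = 98.8%. Illustrations that start from a lower specificity do not fit Table 1; the one above does.
- **Importance.** Accuracy is not among the listed objectives or outcomes, and the planned conclusions on referral, diagnosis and linkage do not depend on it.
- **Preintervention scans.** They avoid referral prompted by a reported score but are still clinician-selected, so they are not an unbiased reference set.

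The main point survives all of these. Nor is it a detail left to a separate analysis plan, because the article itself names the measures and the method.

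**Conclusion.** The concern holds for the sensitivity and specificity of APRI and for both AUROCs, chiefly in intervention-period scans. Sensitivity is biased upward whenever people with cirrhosis and an elevated score are scanned more often than people with cirrhosis and a low score. Specificity is biased downward under the matching condition in people without cirrhosis. The intervention is designed to create that imbalance. The direction for AUROC is not fixed.

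In the illustration, 54% and 99% appear as about 99% and 65%. This rests on assumed PPV, assumed cirrhosis in APRI-negatives and assumed uptake; only 446/37,872 comes from the article. The true size cannot be derived from the document. That only scanned people enter the table is an inference, but it is the only workable reading.

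A reader might infer that the study's main results are compromised, or that NPV is wrong for the same reason. The document supports neither. This is a should-fix on an ancillary analysis.

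**What to change.** Reword the accuracy paragraph in Analysis Methods:

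1. Report the proportion of scanned elevated scorers with confirmed cirrhosis, with a 95% CI and the fraction of elevated scorers who were scanned.
2. Replace the uncorrected sensitivity, specificity and AUROC with verification-corrected estimates, or drop them. Begg-Greenes or inverse-probability-of-verification weighting can use the score, age category, sex and area variables held for all tested people.
3. Report preintervention and intervention scans separately.
4. State that the correction assumes verification depends only on recorded variables, and that preintervention scans are also clinician-selected. Exposure Variables Collected ties liver disease indication to FibroScan requests, so suspicion-driven selection cannot be fully adjusted for.
5. State that verification of low scorers is sparse, so these figures cannot support a claim that the scores exclude cirrhosis in the screened population.

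The cost is a change of wording and analysis, with no new data. The drawback is imprecision. In the illustration about 187 APRI-negatives are scanned and 0.5 cases of cirrhosis are expected among them. Finding none would give a corrected sensitivity of 100%. Finding one would imply 37,426/187 = 200 missed cases and a sensitivity of 111.5/(111.5 + 200) = 36%. If the interval is that wide, dropping the figures is the better choice.

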#### Exposure Variables Collected

Sex, age category (deciles), socioeconomic status of residence (defined by Australian Bureau of Statistics Socio-Economic Index Areas [SEIS] data matched to postcode), urban versus regional place of residence (defined by SEIS data matched to postcode), and liver disease indication recorded on FibroScan requests will be collected.

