### Sample Size Justification

We have conducted a preliminary analysis of the number of AST and platelet count testing events that were performed at St Vincent’s Pathology over a 12-month period (2019). These data showed approximately 11,000 people known to St Vincent’s hospital clinics, and a further 4400 people in the community that had AST and platelet count testing events, that would have allowed APRI calculation to be performed, proving the feasibility of reaching large numbers within the community for cirrhosis screening.

For the comparison of rate of referral for FibroScan before and after the intervention, we estimate that we will be powered to detect a 10% difference in rates of FibroScan referral before and after the intervention. For the logistic regression analyses to determine the difference in proportion of APRI scores leading to referral before and after providing cirrhosis information and FibroScan referral link information (overall and by subgroup), and for determining the proportion of FibroScan referrals that are attended (overall and by subgroup), we are powered to detect a 5% or greater difference between the intervention and historical control groups with power 90% and a sample size of 1100 per subgroup. The above numbers of more than 15,400 individuals having APRI calculations within 12 months suggest that we will be adequately powered to explore our end points including stratified by sex, urban versus rural place of residence, age category, socioeconomic quartile of place of residence, and indication for FibroScan (all of which are expected to have >1000 individuals in each subgroup).

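### Urban/regional residence is assigned by postcode but tested with a person-level chi-square; if elevated scores cluster within postcode, the P value at the elevated-score step will be too small

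*Protocol article*

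**What the plan says.** Exposure Variables Collected defines "urban versus regional place of residence (defined by SEIS data matched to postcode"), so residence is a property of the postcode that each resident inherits. Socioeconomic status is obtained in the same way: "socioeconomic status of residence (defined by Australian Bureau of Statistics Socio-Economic Index Areas [SEIS] data matched to postcode").

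Analysis Methods names the variables for the bivariate comparisons as sex, age category, "urban or regional place of residence [defined by postcode using SEIS data"] and, as a clinical variable, liver disease indication. They are to be "compared with their counterparts using chi-square test for categorical data", across four outcomes: elevated score, FibroScan attendance, elevated FibroScan result and liver clinic attendance. The threshold is fixed for everything: "A 2-tailed *P* value of .05 will be used as the significance threshold for all analyses".

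Outcome Measures sets the unit of analysis: "Data will be analyzed per test event and per individual tested". No section mentions a clustered variance, an area random effect or an area-level analysis. Recruitment confirms that postcode is among the variables collected. The Objectives place these comparisons under the secondary objective, which is worded as describing associated sociodemographic factors.

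**The concern.** A Pearson chi-square treats each person as an independent observation. For sex or age category, which vary within a postcode, that is a reasonable working assumption. Residence is constant within a postcode, so any positive correlation of the outcome among people in the same postcode enters the variance of the urban/regional contrast in full. Such correlation could come from age mix, causes of liver disease or local practice. The chi-square ignores it.

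The elevated-score comparison is the most exposed. It uses everyone tested, so postcodes hold many people, and a very small correlation multiplied by a large cluster size is no longer small. What is at stake is a geographic gradient in elevated APRI or FIB-4 being reported as significant when it reflects only ordinary variation between postcodes.

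**Working it through.** **Plan's own figures.** The article gives no calculation for the residence comparison. The prevalences in its Table 1 reproduce: 816/37,872 = 2.15% (stated 2.2%) for FIB-4 and 446/37,872 = 1.18% (stated 1.2%) for APRI. The only sample-size figure, 1100 per subgroup, is for a before/after difference and has no baseline rate. It matches 13% against 18% (1099 per period, two-sided, 90% power), but nothing below depends on it.

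**Inputs from the article.** N = 37,872 individuals (preintervention), p = 0.0215 for FIB-4, two-sided alpha 0.05.

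**Assumptions, none given in the article.** Number of postcodes K = 100, 300 or 700. ICC from 0.001 to 0.01. Postcode sizes either equal or with a coefficient of variation (CV) of 1.

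**Formulas.** Mean cluster size m = N/K. Design effect DE = 1 + (m − 1) × ICC for equal sizes, and DE = 1 + ((1 + CV²)m − 1) × ICC for unequal sizes. True error of the nominal 5% test = 2 × (1 − Φ(1.96/√DE)).

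**Worked case.** K = 300 gives m = 37,872/300 = 126.2. With ICC 0.005 and equal sizes, DE = 1 + 125.2 × 0.005 = 1.63 and the error is 12.4%. With CV 1, DE = 1 + (252.5 − 1) × 0.005 = 2.26 and the error is 19.2%.

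**Elevated score among all tested.** True error, equal sizes / CV 1:

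| Postcodes (m) | ICC 0.001 | ICC 0.005 | ICC 0.01 |
|---|---|---|---|
| 100 (379) | 9.5% / 13.9% | 24.9% / 37.0% | 37.0% / 50.3% |
| 300 (126) | 6.5% / 8.0% | 12.4% / 19.2% | 19.2% / 29.6% |
| 700 (54) | 5.6% / 6.3% | 8.1% / 11.4% | 11.3% / 17.3% |

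A beta-binomial simulation (4,000 runs per cell, CV 1, 30% of postcodes regional) agrees with the second figure in each cell: 13.4%, 36.5% and 48.7% at 100 postcodes; 7.9%, 18.9% and 28.3% at 300; 5.8%, 11.7% and 18.5% at 700. At ICC 0 it gave 4.6% to 5.0%. DE does not depend on prevalence, so the formula results apply equally to elevated APRI at the same ICC.

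**What the ICCs mean.** The between-postcode SD of prevalence is √(ICC × p(1 − p)). With p(1 − p) = 0.0211 this is 0.46 percentage points at ICC 0.001, 1.03 at 0.005 and 1.45 at 0.01, or about 21%, 48% and 67% of the 2.15% mean. The upper end is therefore a strong assumption.

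**Later steps.** Among the 816 with elevated FIB-4, 100 postcodes gives m = 8.2. At ICC 0.01, DE = 1.07 and the error is 5.8% (6.8% with CV 1; 7.1% in the simulation, which assumed 30% attendance). Among the 446 with elevated APRI, m = 4.5, DE = 1.04 and the error is 5.4% (5.9% with CV 1). More postcodes or a lower ICC bring these closer to 5%.

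**Does the remedy work?** In simulations of the elevated-score step with 100 to 700 postcodes, a variance clustered on postcode gave error between about 4.6% and 7.2%. It rose to about 9% with 100 postcodes split 75/25.

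**The case against.** The comparison is unadjusted, secondary and descriptive, in a pilot, and no decision rule depends on it. Postcodes were not sampled: everyone eligible is included, so describing the people tested in this catchment is a legitimate target that needs no cluster variance. The article condenses a fuller plan, where variance options usually sit. All of this lowers the stakes. It does not remove the point, because the article names the test and attaches a significance threshold to it. A P value of .05 invites inference beyond the people counted.

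A reader might also infer more than the text supports:

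- **That the P values are certainly too small.** This depends on an ICC that the article does not give. At ICC 0 the chi-square is valid, and with 700 postcodes and ICC 0.001 the excess is about one percentage point.
- **That a larger conventional ICC, such as 0.05, applies.** The postcode SD would then be about 3.2 percentage points, larger than the 2.15% mean. Nothing in the article suggests such heterogeneity.
- **That socioeconomic status is tested in the same way.** It is collected, and it appears in Sample Size Justification among analyses "stratified by sex, urban versus rural place of residence, age category, socioeconomic quartile of place of residence", but it is not in the Analysis Methods list of variables for these comparisons.
- **That the 1100 per subgroup must be inflated or restated in postcodes.** That figure concerns intervention against historical control. Period varies within each postcode, so the full design effect does not apply to it.

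**Conclusion.** The point holds in a limited form. A named person-level test is applied to a named postcode-level exposure, with no stated allowance for clustering. The consequence is conditional on clustering and is confined in practice to elevated APRI/FIB-4 among all tested. There the true error of the nominal 5% test is about 6% to about 50% over 100 to 700 postcodes and ICC 0.001 to 0.01. Both ranges are assumptions, and the upper end needs few postcodes, the largest ICC and unequal postcode sizes. For FibroScan attendance, cirrhosis-range result and clinic attendance, the same ICC range leaves the error at about 5% to 7%, which is not a reason for concern. The primary outcomes are not affected.

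**What to change.** In Analysis Methods, for urban/regional residence, replace the ordinary chi-square with a logistic model whose variance is clustered on postcode, or with a Rao-Scott chi-square that takes postcode as the cluster. State that socioeconomic quartile will be handled in the same way if it is tested. Keep the ordinary chi-square for sex and age category. Sample Size Justification needs no change on this account.

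The cost is one sentence of analysis wording and one option in the Stata software already named. Postcode is already collected. Intervals for residence contrasts will be somewhat wider; if there is no clustering, little is lost.
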